#### Data collection and management

Table 2 shows the schedule of enrollment, interventions, and assessments. Feasibility outcomes will be evaluated throughout the course of the study. Other data will be collected online using questionnaires presented in an online format.^2^ Measurements will be taken at baseline (T_0_), immediately after the intervention (T_1_), and 3 weeks after the intervention (T_2_). Participants will complete the baseline measurement by scanning a two-dimensional code to obtain their questionnaire. At T_1_ and T_2_, the questionnaires will be sent to participants by WeChat. All participants will receive up to two reminders to complete the T_1_ and T_2_ measurements, regardless of protocol adherence or any previously uncompleted online questionnaires. Participants will be informed that they will receive a gift after completing the online questionnaires to promote retention.

**TABLE 2 T2:** SPIRIT figure, schedule of enrollment, interventions, and assessments.

	Study period				
	
	Enrollment	Allocation	Post-allocation		
			
			Intervention		

Timepoint	T_0_	0	0	T_1_	T_2_
**Enrollment:**					
Eligibility screen	×				
Informed consent	×				
Allocation		×			
**Intervention**					
Intervention group (WeChat-based self-compassion training)					
Control group (WeChat-based psychological health education)					
**Instruments**					
Demographic and other personal data	×				
**Primary outcomes**					
Patient adherence	×			×	×
**Secondary outcomes**					
Self-compassion	×			×	×
Stigma	×			×	×
Social suppor	×			×	×
Program feasibility				×	
Program acceptability				×	

Online website servers will be used to collect all data, according to the hospital security guidelines and policies; all web-based information transmission will be encrypted. Baseline data and follow-up data will be saved first on the website and then wirelessly uploaded into an Excel database via an Internet server. Data entry will be accomplished by individuals external to the research team, and data analysis will be completed without referring to the allocation information.

#### Statistical methods

The baseline characteristics of the sample will be compared using χ^2^-tests for categorical variables and Student’s *t*-test or Mann–Whitney *U*-test for quantitative variables.

Statistical analyses will be performed on the basis of the intention-to-treat approach, which will include all randomized participants. The extent of missing data will be analyzed. We will explore missing data patterns and determine the type of missing data (missing completely at random, missing at random, and not missing at random). We will use multiple imputations to substitute missing values and conduct sensitivity analyses for datasets with and without imputed data.

Descriptive statistics will be used to evaluate study feasibility and acceptability. We will use linear mixed models with time (pre-intervention vs. post-intervention measures) as a within-group effect, study condition (intervention condition vs. control condition) as a between-group effect, and the interaction effect between these two effects to evaluate the efficacy of the WeChat-based self-compassion training intervention on patient adherence, self-compassion, stigma, and social support. This primary analysis will be performed using the data from the baseline and 3-week post-assessment. We will conduct within-group analyses using repeated measures ANOVA (pre-intervention, post-intervention, and follow-up measures) and paired *t*-tests when comparing only two time points to analyze the stability of the short-term effects of the intervention on patient adherence, self-compassion, stigma, and social support. Moreover, the correlation among self-compassion, stigma, social support, and patient adherence will be analyzed using Pearson correlation. The results will be reported with 95% confidence intervals. Bilateral *p* ≤ 0.05 shows a statistically significant difference. All data will be analyzed using SPSS 24.0.

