#### Sample size

The sample size of the study was calculated using the G*Power 3.1 software package (Faul et al., 2007). With a power of 0.80, an alpha set at 0.05, and an effect size of 0.3 for the primary outcome, the Medication Adherence Rating Scale (MARS) score (Çetin and Aylaz, 2018), it was determined that each group would need 176 patients with schizophrenia. Given an attrition rate of 10%, a minimum of 392 participants (196 in each group) is required.

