### Limitations

Although we have carefully crafted this protocol, this study has some limitations. First, this intervention will be conducted for 3 weeks, and some participants may not be able to complete the study because of changes in their emotions or loss of follow-up. Second, we may not be able to avoid participation bias, as participation in the study is voluntary. Third, restricting the study to patients with a smartphone and being able to use it may cause a selection bias, which could reduce the generalizability of our results. This limitation is common in online intervention. Finally, we will not be able to monitor the level of usage of the WeChat public accounts during the trial because of the limited function of the WeChat public account; therefore, determining the extent to which higher intervention adherence is associated with higher benefits on outcomes will not be possible.

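### The plan promises to determine whether data are missing at random or not, which observed data cannot show, and the sensitivity analysis it names does not examine data missing not at random (MNAR).

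*Protocol article*

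**What the plan says.** All statements on missing data stand in the Protocol article, Statistical methods.

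- The analysis follows an "intention-to-treat approach, which will include all randomized participants".
- After describing the extent and patterns of missing data, the team will "determine the type of missing data (missing completely at random, missing at random, and not missing at random".
- Handling and sensitivity analysis share one sentence: "We will use multiple imputations to substitute missing values and conduct sensitivity analyses for datasets with and without imputed data".
- The primary analysis is a mixed model: "We will use linear mixed models with time (pre-intervention vs. post-intervention measures) as a within-group effect", with study condition and the time-by-condition interaction. Repeated-measures ANOVA and paired t-tests follow for within-group change.

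No analysis is made to depend on which mechanism is found, and no analysis under MNAR is named.

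Other sections bear on why data may be missing. Abscission criteria counts as dropout a worsening mental state, quitting, lost contact with tasks not done, and a missed post-intervention evaluation. Limitations adds that "some participants may not be able to complete the study because of changes in their emotions or loss of follow-up". Data collection and management provides up to two reminders at each follow-up, whether or not the participant kept to the protocol, and a gift for completing the questionnaires.

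**The concern.** MAR and MNAR differ only in the values nobody sees, so no procedure applied to the recorded data can decide between them. Exploring patterns and testing against MCAR is sound; the further step is not available.

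The named sensitivity analysis does not fill the gap. If imputed and unimputed results agree, a reader may take this as reassurance about informative dropout, when both versions of the primary model make the same MAR assumption.

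This matters because the primary outcome is self-reported medication adherence, collected by online questionnaire. A patient who stops answering may well be one who has stopped taking medication. The arms also differ in burden: three daily tasks, including a written journal, against reading alone. Loss could therefore differ between arms, and its effect need not cancel in the treatment contrast.

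**Working it through.** **1. The plan's own figures.** Sample size states: "With a power of 0.80, an alpha set at 0.05, and an effect size of 0.3 for the primary outcome". Statistical methods makes the test two-sided: "Bilateral *p* ≤ 0.05 shows a statistically significant difference". Reading 0.3 as a standardised mean difference, the two-sample t-test needs 175.38, rounded up to 176 per group. Allowing for 10% attrition, 176 / 0.90 = 195.6, so 196 per group and 392 in total. These figures reproduce and are not in dispute.

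**2. Can the mechanism be determined?** One million records were simulated with a baseline value and an outcome correlated 0.5, both in SD units. Missingness depended on baseline only (MAR) and came to 10.7%. A second, MNAR, version kept every observed value and the same pattern of missingness, but lowered each unseen outcome by 0.5 SD. The observed data are identical by construction. The full-data means are 0.001 and −0.052 SD, a gap of 0.107 × 0.5 ≈ 0.054. No test on the observed data can tell the two apart.

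**3. What does the named comparison vary?**

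| Analysis | With imputation | Without imputation |
|---|---|---|
| Primary mixed model | MAR (standard multiple imputation) | MAR (likelihood on available data) |
| Repeated-measures ANOVA, paired t-tests | MAR | complete cases, towards MCAR, which is stricter |

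The second row does change the assumption, but away from MNAR. Neither row examines MNAR.

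**4. How large could the effect be?** Let m be the missing fraction in an arm and δ the shortfall of its missing outcomes, in SD, beyond what the observed data predict.

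Bias in the treatment contrast = m(intervention) × δ(intervention) − m(control) × δ(control).

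Only m = 10% comes from the documents. The 20% and every δ are assumptions. With a shortfall in the intervention arm only and an effect of 0.3 under MAR, the adjusted effect is 0.3 − m × δ. Power is approximated from a simple two-group comparison with 196 × (1 − m) per arm.

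| m | δ (SD) | Bias (SD) | Bias / 0.3 | Adjusted effect | Approx. power |
|---|---|---|---|---|---|
| 10% | 0 | 0 | 0% | 0.300 | 80% |
| 10% | 0.25 | 0.025 | 8% | 0.275 | 73% |
| 10% | 0.5 | 0.05 | 17% | 0.250 | 65% |
| 10% | 1.0 | 0.10 | 33% | 0.200 | 47% |
| 20% | 0 | 0 | 0% | 0.300 | 76% |
| 20% | 0.25 | 0.05 | 17% | 0.250 | 60% |
| 20% | 0.5 | 0.10 | 33% | 0.200 | 43% |
| 20% | 1.0 | 0.20 | 67% | 0.100 | 14% |

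With equal m and δ in both arms, the bias is m × δ − m × δ = 0.

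**5. Where would a result tip?** Suppose the MAR estimate were exactly 0.3.

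- At 10% missing, SE = √(2/176.4) = 0.1065. Significance is lost when 0.3 − 0.1δ falls below 1.96 × 0.1065 = 0.209, that is, at δ of about 0.91 SD.
- At 20% missing, SE = √(2/156.8) = 0.1129 and the threshold is 0.221, so δ is about 0.39 SD.

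These standard errors ignore any gain from baseline adjustment and the extra variance from imputation, so they show scale only.

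**The case against.** The strongest reply is that the faulty phrase drives nothing. Multiple imputation is fixed whatever mechanism is found, so deleting a few words would cure it, and an MNAR analysis with its grid of shifts is normally left to the statistical analysis plan. The first half stands: the consequence of the phrase alone is small. The second half does not dispose of the point, because the article itself chooses a sensitivity analysis, to "conduct sensitivity analyses for datasets with and without imputed data", and that choice does not address the mechanism it says it will identify.

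Four stronger readings are tempting, and the documents do not support them.

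- *The protocol expects MNAR loss.* Limitations says only that loss may follow emotional change, and does not tie it to unseen MARS values. Distress is asked about weekly, and self-compassion, stigma and social support are measured; loss explained by recorded data would be MAR.
- *The plan would declare its result robust.* No section says so or sets a rule for it.
- *Heavier burden must produce unequal loss.* Reminders go to participants regardless of adherence to the protocol, and the gift may help too. Both may reduce the loss, though neither rules it out.
- *Two thirds of the target effect is at risk.* The 67% needs twice the planned attrition, a 1 SD residual shift and an effect confined to one arm, all assumed.

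It is also fair that the with/without comparison has some use for the ANOVA and t-tests, and that the trial describes itself as exploratory.

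**Conclusion.** The point holds in limited form. The statement that the type of missing data will be determined cannot be carried out as regards MAR against MNAR, and the one sensitivity analysis named leaves MNAR unexamined. Outcome-related loss is plausible from the article's own dropout reasons, but is not stated as expected.

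At the planned 10% attrition the possible bias is modest: 0 to 0.10 SD for residual shifts of 0 to 1 SD in one arm. It becomes material if attrition exceeds the plan, reaching 0.20 SD at the extreme of the assumed 20% range. It is zero if missingness and shift are equal across arms. The size rests on assumed shifts and on reading 0.3 as a standardised difference; the logical part rests on neither. The primary analysis can stand. The change should be made because it repairs a stated method at little cost.

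**What to change.** In Statistical methods:

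1. Replace the promise to determine the type of missing data with a description of patterns and reasons for missingness by arm, and a check against MCAR.
2. State MAR as the assumption of the primary analysis.
3. Keep the with/without-imputation comparison as a supplement.
4. Add a delta-adjusted (tipping-point) analysis of MARS. Starting from the MAR-imputed datasets, shift imputed values towards poorer adherence by 0, 0.25, 0.5, 0.75 and 1.0 SD, first in the intervention arm only and then in both arms. Report the shift at which the conclusion changes.

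The cost is a few lines of code on datasets that will exist anyway, and one more table. No new data or design change is needed. The downside is that the result may look less robust than the present comparison would suggest.

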#### Recruitment, randomization, and allocation

Potential participants in the hospital will be identified by screening the electronic medical records on each psychiatric ward to determine those who have achieved a curative effect that meets the clinical recovery standard. These potential participants will then be contacted by a research coordinator to determine their eligibility, their ability to fill in the questionnaire, their interest in participation, their experience using WeChat, and their willingness to sign the consent form (including one of their family members). The aims of the study and participants’ right to withdraw at any time will be explained to eligible participants verbally and via an information sheet. Individuals will be able to ask the research coordinator questions about the study.

After signing the written informed consent and completing the basic demographic questionnaire and baseline evaluation, all eligible participants will be randomized to either the intervention group or the control group at a 1:1 ratio. Participants will be randomized individually using a computer-generated sequence of random numbers generated with SPSS 25. Allocation concealment will be achieved through sequentially numbered, opaque, sealed envelopes. The random sequence will be generated by an independent researcher not involved in patient enrollment and the baseline assessment. The envelope will only be opened after obtaining consent, confirming the patient’s eligibility, and performing the baseline evaluation. Then, the responsible clinical psychiatric nurses, who will facilitate the intervention in this study, will be informed of the intervention allocation. Given that the participants will either receive direct access to the WeChat-based self-compassion training or the WeChat-based psychological health education, participants will be blind to their allocation.

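### The primary group-by-time contrast leaves the pre-randomization baseline difference free, so it is less precise than a baseline-adjusted comparison, and the stated 80% power is not tied to it

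*Protocol article*

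**What the plan says.** **Primary model** (Statistical methods): "We will use linear mixed models with time (pre-intervention vs. post-intervention measures) as a within-group effect". Study condition is the between-group effect, and the interaction of the two is included to judge efficacy. The same section limits the primary analysis to baseline and one post-assessment, so the model has two time points. Condition enters as an ordinary effect, and nothing constrains the arms to be equal at baseline.

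**Order of events** (Recruitment, randomization, and allocation): "The envelope will only be opened after obtaining consent, confirming the patient’s eligibility, and performing the baseline evaluation".

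**Sample size** (Sample size): "The sample size of the study was calculated using the G*Power 3.1 software package", with the inputs "With a power of 0.80, an alpha set at 0.05, and an effect size of 0.3 for the primary outcome", that outcome being the MARS score. The result is that "it was determined that each group would need 176 patients with schizophrenia", raised to 196 per group (392 in total) for 10% attrition. The section names no test, no time point, no SD behind the 0.3 and no correlation between baseline and follow-up MARS. Sidedness comes from Statistical methods: "Bilateral *p* ≤ 0.05 shows a statistically significant difference".

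**The concern.** Two things are at stake.

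- **Precision.** Baseline is measured before allocation, so the true baseline difference between arms is zero in expectation. A model with a free condition effect still estimates that difference and subtracts it in full. This adds noise that baseline adjustment would mostly remove.
- **Meaning of the 80%.** The precision of a change-score contrast depends on the correlation between the two MARS measurements. The sample-size section gives no correlation and does not name the test. A reader cannot tell whether the stated power refers to the primary analysis. On one reading of the 0.3, that analysis has less than 80% power when the correlation is below about 0.5.

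**Working it through.** **Inputs.** From Sample size: power 0.80, alpha 0.05, effect size 0.3, 176 per group, 10% attrition. From Statistical methods: two-sided testing, two time points, and the terms time, condition and interaction. The correlation rho is not in the document, so 0.3 to 0.7 is shown as an assumed range. The calculations also assume complete data and the same SD, sigma, at both times.

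**1. Reproducing the plan's figure.** For a two-sided two-sample t-test with d = 0.3 and n per arm, the noncentrality is 0.3 × sqrt(n/2). The smallest n giving 80% is 176 (power 0.801). Then 176/0.9 = 195.6, rounded up to 196 per arm and 392 in total. The plan's figures are reproduced exactly. A one-sided test (138 per arm), a Mann–Whitney test (about 184 per arm), a one-way ANOVA with f = 0.3 (90 in total) and the G*Power within-between interaction settings tried (f = 0.3, 0.15 or 0.1; two or three time points; rho 0 to 0.7) do not give 176 per arm.

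**2. Variance of the planned contrast.** With two time points the interaction is the arm difference in mean change.

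- Variance of change per patient: 2 × sigma² × (1 − rho)
- Residual variance after adjusting for baseline: sigma² × (1 − rho²)
- Ratio: 2(1 − rho) / [(1 − rho)(1 + rho)] = 2/(1 + rho), which exceeds 1 for every rho below 1

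**3. Power at 176 per arm if 0.3 is in SDs of the score.** The effective d is 0.3/sqrt(2(1 − rho)) for the interaction and 0.3/sqrt(1 − rho²) after baseline adjustment. At rho 0.3, for example, these are 0.3/1.183 = 0.254 and 0.3/0.954 = 0.314.

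| rho | Extra variance of planned contrast | Power, planned interaction | Power, baseline-adjusted |
|---|---|---|---|
| 0.3 | 54% | 66% | 84% |
| 0.4 | 43% | 73% | 86% |
| 0.5 | 33% | 80% | 90% |
| 0.6 | 25% | 88% | 94% |
| 0.7 | 18% | 95% | 98% |

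The interaction reaches 80% at rho of about 0.50 with 176 per arm, or about 0.44 if all 196 per arm are observed. With all 196 observed, power at rho 0.3 is 71%. The baseline-adjusted analysis has 80% at rho 0 and more above it.

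**4. Power at 176 per arm if 0.3 is in SDs of the change.** The interaction is then a t-test at d = 0.3, so power is 80% at any rho. After baseline adjustment the effective d is 0.3 × sqrt(2/(1 + rho)), which gives 94% at rho 0.3, 90% at 0.5 and 86% at 0.7.

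**The case against.** A reader might infer that the trial was powered for a single post-intervention score, that the primary analysis is therefore a different test from the one powered, and that 392 is too few. The document does not support this. It names neither the test nor the SD, and a t-test on change scores with 0.3 in change SDs gives the same 176. With two time points, that is the planned interaction test. The wording "an effect size of 0.3 for the primary outcome, the Medication Adherence Rating Scale (MARS) score" makes the score reading more natural but does not settle it. Even on that reading no shortfall is shown: no correlation is given, and above about 0.5 the planned analysis exceeds 80%. The threshold also depends on how many patients are observed. The analysis is to include everyone randomized, but imputation does not restore full information, so the threshold lies between 0.44 and 0.50.

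It can also be said that, under randomization, the interaction is a valid and unbiased estimate, that the trial is described as exploratory, and that a condensed article may leave the SD and correlation to the full protocol. The first is true, so this is a matter of efficiency and not of bias. The last tempers the criticism of the sample-size section. Neither removes the precision point, because the article does not leave the primary model open: it fixes the terms and the time points, and the chosen form uses the baseline data less well than an equally simple alternative.

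**Conclusion.** The concern holds in two parts of different strength.

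- **Firm.** As written, the primary contrast is less precise than a baseline-adjusted one on either reading of the 0.3. The excess variance is 54%, 33% and 18% at rho 0.3, 0.5 and 0.7. This rests on baseline preceding allocation, which the article states, and on equal variances and complete data, which are assumptions.
- **Conditional.** If 0.3 is in score SDs and rho is below about 0.50 (0.44 with no attrition), the planned analysis has less than the stated 80%. If 0.3 is in change SDs, the 80% stands whatever rho is. The document does not allow a choice between these readings.

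The change is worth making before the data are analysed because it improves power on both readings. The target of 392 need not be revisited on this ground.

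**What to change.** 1. In Statistical methods, make the primary estimate the post-intervention arm difference in MARS adjusted for baseline MARS. Use either ANCOVA or the same mixed model with the arm means constrained equal at T0.
2. In Sample size, have the sponsor state which test was used and whether the 0.3 is in SDs of the score or of the change, so that the 80% refers to the primary analysis. The sponsor must supply this. Writing in an effect of 0.3 on the post score would be wrong if the figure was in change SDs.

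The cost is a change of wording. Baseline MARS is already collected at T0, and no extra patients, visits or data are needed.

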#### Primary aim

To evaluate the effects of the WeChat-based self-compassion training on treatment adherence, relative to the control WeChat-based psychological health education.

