### Design

#### Trial design

The study will be an exploratory, parallel randomized controlled trial (RCT) comparing a 3-week WeChat-based self-compassion training protocol to a control condition with only WeChat-based psychological health education. The effects of the intervention on treatment adherence, self-compassion, stigma, and social support will be evaluated among patients with schizophrenia. Eligible participants will be randomly allocated to one of the two conditions (intervention or control) at a ratio of 1:1. The Consolidated Standards of Reporting Trials (CONSORT) (Schulz et al., 2010) flowchart is presented in Figure 1. The study protocol was developed and reported according to the Standard Protocol Items: Recommendations for Interventional Trials (SPIRIT) 2013 statement (Chan et al., 2013; Supplementary File 1).

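### The arms are compared at only one post-baseline visit; maintenance of effect at the other (T2 on the natural reading) rests on within-arm tests alone

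*Protocol article*

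**What the plan says.** All references are to the Protocol article.

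- **Schedule** (Data collection and management): "Measurements will be taken at baseline (T_0_), immediately after the intervention (T_1_), and 3 weeks after the intervention (T_2"). Table 2 lists "Patient adherence", the primary outcome, at all three visits, and likewise self-compassion, stigma and social support.
- **Programme length** (Trial design): the trial is described as "comparing a 3-week WeChat-based self-compassion training protocol to a control condition".
- **Primary aim**: the effect on "treatment adherence, relative to the control WeChat-based psychological health education". The aim is comparative.
- **Between-arm analysis** (Statistical methods): "linear mixed models with time (pre-intervention vs. post-intervention measures) as a within-group effect", study condition as the between-group effect, and their interaction. The next sentence limits the data: "This primary analysis will be performed using the data from the baseline and 3-week post-assessment".
- **Analysis of all three visits** (Statistical methods): "We will conduct within-group analyses using repeated measures ANOVA (pre-intervention, post-intervention, and follow-up measures"), plus paired t-tests when only two time points are compared. The stated purpose is "to analyze the stability of the short-term effects of the intervention on patient adherence, self-compassion, stigma, and social support".

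No other section adds a comparison of the arms at the visit left out of the mixed model.

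**The concern.** Both arms are randomised and both are measured at T2, yet on the natural reading the randomised comparison stops at T1. What happens afterwards is to be judged from change inside each arm. That change mixes any effect of the training with time, attention and regression to the mean. Participants are recruited on psychiatric wards once they meet the clinical recovery standard, so drift common to both arms is plausible.

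The within-arm tests also answer a different question from the one put to them. If the intervention arm stays flat from T1 to T2 while the control arm catches up, the intervention arm looks stable although the arm difference has gone. If both arms decline equally, each looks unstable although the difference is fully maintained.

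At stake is any statement that the effect lasts. The Conclusion section says the programme will be implemented in hospitals and communities if it is effective, and durability bears on that decision.

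**Working it through.** **1. Visits against analyses (taking the post point as T1)**

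| Visit | Measured in both arms | Between-arm model | Within-arm tests |
|---|---|---|---|
| T0 | yes | yes | yes |
| T1 | yes | yes | yes |
| T2 | yes | no | yes |

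**2. Which visit is the post point?** The mixed model contrasts pre-intervention with post-intervention measures. Two sentences later the plan lists post-intervention and follow-up as separate measures. With a 3-week programme and T1 immediately after it, the label in "This primary analysis will be performed using the data from the baseline and 3-week post-assessment" most naturally means T1. But T2 is itself defined as 3 weeks after the intervention, and nothing ties the label to T1 or T2. If T2 were meant, T1 would be the visit without a between-arm test. Either way one visit has none.

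**3. The plan's own figure.** Inputs from Sample size: effect size 0.3, power 0.80, alpha 0.05; two-sided from Statistical methods. For a two-sample t-test the noncentrality is 0.3 × √(n/2). Power is 0.799 at n = 175 and 0.801 at n = 176, so 176 per group reproduces. With 10% attrition, 176 / 0.90 = 195.6, rounded up to 196 per group and 392 in total, which also reproduces. The size rests on one two-group comparison.

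**4. Within-arm tests when the arms do not differ (illustration).** The document gives neither drift nor correlation, so both are assumed. Let both arms change by g SD from T0 to T2, with correlation ρ and 176 per arm. In SD units:

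- SD of change = √(2(1 − ρ)), which is 1 at ρ = 0.5
- noncentrality = g × √176 / SD of change, on 175 degrees of freedom
- P(intervention improves significantly, control not significant) = P(significant improvement) × (1 − P(significant in either direction)), because the arms are independent

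At ρ = 0.5:

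| Common drift g | Noncentrality | P(an arm improves significantly) | P(intervention improves significantly, control not) |
|---|---|---|---|
| 0 | 0 | 0.025 | 0.024 |
| 0.10 | 1.327 | 0.261 | 0.193 |
| 0.15 | 1.990 | 0.508 | 0.250 |
| 0.20 | 2.653 | 0.751 | 0.187 |
| 0.25 | 3.317 | 0.910 | 0.082 |
| 0.30 | 3.980 | 0.977 | 0.022 |

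The range is about 2% to 25%. At the same drifts it is 2.4% to 23.9% for ρ = 0.3 and 0.1% to 24.0% for ρ = 0.7. A two-sided 5% between-arm test falsely favours the intervention 2.5% of the time whatever the common drift. At 0.3 SD the discordant pattern is rare only because both arms are nearly always significant: the intervention arm then improves significantly 98% of the time with no effect of the intervention.

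**5. A non-significant T1-to-T2 test is not stability.** Suppose the intervention arm loses 0.15 SD between T1 and T2, half the planned effect of 0.3, with T1-T2 correlation 0.5 (assumed). The noncentrality is again 0.15 × √176 / 1 = 1.990 and the power is 0.508. The loss would be missed in 1 − 0.508 = 49% of trials. With correlation 0.7 the power is 0.724, and it would be missed in 28%.

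**6. A between-arm contrast at T2.** With 176 evaluable per arm and a difference still at 0.3, step 3 gives power 0.80 at two-sided 0.05. As a secondary analysis it needs no more patients.

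**The case against.** The strongest reply is that the primary question is handled properly. The effect on adherence relative to control is tested by a group-by-time interaction, which is a valid between-arm test. Durability is not among the listed aims, the trial calls itself exploratory, and T2 is collected in both arms, so a T2 contrast can be added without changing conduct. All of that stands, and it limits the weight of the point.

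Three stronger readings are tempting, and the document does not support them.

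- **That the primary visit is left open, so the better of T1 and T2 could be called primary with an inflated error rate.** The wording in Statistical methods points to T1, and nothing provides for choosing between visits. What remains is a loose label.
- **That the percentages in step 4 are the plan's false-positive rate.** The plan never says that efficacy or durability will be inferred from one arm being significant and the other not. The figures also depend on assumed drift and correlation, and at the ends of the range at correlation 0.5 they do not exceed 2.5%.
- **That the primary result or the sample size is compromised.** The primary model is a randomised comparison, and the stated size reproduces.

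It may also be said that an unseen analysis plan or full protocol could cover T2. That would answer a missing detail. Here the article states which data the between-arm model uses and assigns the three-visit analysis to within-arm tests for a stated inferential purpose. That is a choice of method, and the method does not fit the purpose.

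**Conclusion.** The point holds in a limited form. The only stated between-arm analysis uses baseline and one post-baseline visit, most naturally T1. The other visit enters only within-arm tests, which cannot show that a difference between arms is maintained. This conclusion follows from the text and needs no assumed figure. The 2% to 25% range (176 per arm, correlation 0.5, common drift 0 to 0.3 SD, no arm difference) illustrates how uninformative a contrast of within-arm significance can be. It is not an error rate of the plan.

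The label of the post visit needs clarifying but is not an open choice. The primary T1 comparison and the sample size of 392 are unaffected. This should be fixed, but it is not a condition for the validity of the primary analysis.

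**What to change.** In Statistical methods:

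1. Name the primary contrast by visit label, for example the group-by-time contrast from T0 to T1.
2. Add the between-arm group-by-time contrast at the other visit, with its 95% CI, as a secondary analysis. It can come from one linear mixed model on T0, T1 and T2 with time as categorical, or from a separate T0-to-T2 contrast. Either is valid.
3. Base any statement on durability on that contrast and its interval.
4. Keep the repeated measures ANOVA and paired t-tests as description within each arm, not as evidence of an effect or of its stability.

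The cost is a few sentences: no new data, no extra patients and no change of software. The sponsor must commit to one primary visit by name, and this should be done before outcome data are seen.
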